## Abstract

**Introduction::**

Major depressive disorder (MDD) is a common condition worldwide, and leads to degradation in quality of life and large socioeconomic costs. There has been increasing demand for new therapies with fewer side effects. SOCG (SOCG tablet) is a modified prescription of So-ochim-tang, which is widely used in Traditional Korean Medicine to treat MDD. We aim to evaluate the efficacy of SOCG in treating MDD, and identify the optimum dose.

**Design::**

The protocol we are following is that of a Phase II clinical trial with a randomized, double blinded, placebo controlled, and parallel design. One hundred forty-eight participants will be randomly divided into 4 groups and treated for 8 weeks.

**Outcome measures::**

The primary outcome will be the score in the Korean Version of the Hamilton Depression Rating Scale. Scores in the Korean version of the Beck Depression Inventory-II Korean Symptom Check List-95 (KSCL-95), State Trait Anxiety Inventory-Korean version, State- Trait Anger Expression Inventory- Korean version (STAXI-K), Insomnia Severity Index (ISI), and the EuroQol-5 Dimension (EQ-5D) will be considered as secondary outcomes.

**Discussion and Conclusions::**

Demonstration of human safety and efficacy of SOCG in the present trial and identification of the appropriate dose will justify a New Drug Application and a phase III clinical trial. Further, we expect that this new antidepressant will be able to increase cure rates, and alleviate the burden of medical expenses.

**Trial registration number::**

Clinical Research Information Service, Republic of Korea (KCT0002763).

## Introduction

1

Depressive disorders influence general social functions and quality of life, manifesting as depression, lack of concentration, impaired judgement, fatigue, and changes in mood, cognition, and movements.^[1]^ This group of disorders includes disruptive mood disorder, dysregulation disorder, major depressive disorder (MDD), persistent depressive disorder, and various diseases with depression. In general, MDD^[2]^ is considered to be representative of depressive disorders. MDD is defined as single or recurrent episodes of major depression, without episodes of mania or hypomania.^[3]^

The WHO announced that 322 million people have depressive disorders in the year 2015, comprising 4.4% of the world's population.^[4]^ Depressive disorders result in significant social losses including treatment costs, family burden, and workplace inefficiency.^[5]^ Severe obstacles in carrying out social or vocational functions are present, especially if MDD begins in the early 20s to 30s. In Korea, the associated socioeconomic costs have gradually increased to 9.135 billion US dollars in 2011.^[6]^ In the United States, the economic burden of depression was estimated at 187.3 billion US dollars in 2010.^[7]^ MDD is known to relapse in 60% to 70% patients with more frequent episodes being associated with a higher probability of relapse. The recurrence rate 2 years after initial treatment is 25% to 40%, increasing to 60% in 5 years, 75% in 10 years, and 87% in 15 years.^[8]^

However, MDD may have favorable prognosis when properly treated at the early stage. Antidepressants considerably reduce risks of MDD relapse, and comprise a large portion of the pharmaceutical market worldwide, occupying the 3rd place among single drugs and valued at almost 132 million dollars in 2014 in Korea. Further, the demand for anti-depressants is increasing as MDD frequently co-occurs with neuropsychiatric diseases including panic disorder, social phobia, post-traumatic stress disorder, or general anxiety disorder.^[9]^ The market size is expected to gradually expand by 10% to 15% annually.^[10]^ At present, serotonin norepinephrine reuptake inhibitors (SNRIs), noradrenaline reuptake inhibitors (NARIs), and norepinephrine and dopamine reuptake inhibitor (NDRIs) have been developed as antidepressants. In Korea, selective serotonin reuptake inhibitors (SSRIs) are the antidepressants most commonly prescribed by clinicians.^[8]^

SSRIs and tricyclic antidepressants (TCAs) have been reported to have significant antidepressant effects along with various side effects. The most common side effects of SSRIs are nausea, vomiting, diarrhea, stomach ache, hot flashes in the chest, and headache. 10% to 20% of patients experience insomnia, anxiety, and excitement, and 30% to 40% experience sexual dysfunction such as retarded ejection, erectile dysfunction, and decreased sexual desire. TCAs usually cause depersonalization, confusion, orthostatic hypotension, and sedation as initial symptoms and cloudy vision, severe thirst, weight gain, epilepsy, and extrapyramidal symptoms as later symptoms.^[8]^ In addition, Koreans are known to be 4 times poorer metabolizers via the hepatic enzymes compared to western populations, increasing the likelihood of toxicities.^[11]^ Therefore, new antidepressants suitable for use by Koreans are needed. In this regard, natural products have recently been receiving attention which have been due to their proven safety and effectiveness based on clinical experience. Herbal decoctions described in various Korean classical medical texts have shown effectiveness in treating MDD in clinical settings.

SOCG is a prescription containing So-ochim-tang combined with *Platycodonis Radix* and *Aurantii Fructus Immaturus*. So-ochim-tang is widely used for treatment of MDD and somatization disorder, which are thought to be caused due to stagnation of qi. Its use is mentioned in “Donguibogam”^[12]^ (“So-ochim-tang for … every qi-related problem”) to treat qi-related pains in the chest and abdomen. SOCG has been shown to have reasonable antidepressant activity in animal behavior studies compared to different antidepressant treatments. It has also been patented as a composition for treating depressive disorder^[13,14]^ (Registered patent of Republic of Korea 10-1910013). However, clinical effects in humans through well-designed trials have not been assessed.

In the present study, we aim to assess the efficacy and safety of orally administered SOCG in MDD patients and determine the appropriate dosage.

## Methods and materials

2

### Study design and setting

2.1

The study is designed as a Phase II clinical trial and is following a randomized, double blinded, placebo controlled, parallel design to examine the efficacy of SOCG in MDD treatment.

Participants will be selected from volunteers based on demographic information, medical history, vital signs, lab examinations, and selection criteria. Selected participants will be assigned to 3 experimental groups and 1 placebo group according to the stratified block randomization. The experimental groups will be a low dose group, a medium dose group, and a high dose group. Participants will be given SOCG or placebo 3 times/day, for 8weeks (56 days). They will be examined using the Korean Version of the Hamilton Depression Rating Scale (K-HDRS), the Korean version of the Beck Depression Inventory-II (K-BDI-II), Korean Symptom Check List-95 (KSCL-95), State Trait Anxiety Inventory-Korean version (STAI-K), State Trait Anger Expression Inventory Korean version (STAXI-K), Insomnia Severity Index (ISI), Instrument on Pattern Identifications for Depression, EuroQol-5 Dimension (EQ-5D), and melatonin and cortisol levels to assess score variation, improvements in quality of life, and biological indicators.

The research progress is summarized in Figure 1 and the examination details followed by visit schedules are shown in Table 1. Each visit should occur at the scheduled date or within ±4 days. The screening tests will be completed 10 days before the second visit (0 week). The results will be examined at the second visit. The lab tests will include hematologic tests for levels of hemoglobin, hematocrit, red blood cell count, white blood cell count, platelet count, and erythrocyte sedimentation rate, and hematochemical tests for levels of aspartate aminotransferase (AST), alanine aminotransferase (ALT), gamma-glutamic transpeptidase (γ-GTP), alkaline phosphatase (ALP), blood urea nitrogen (BUN), creatinine, total bilirubin, glucose, Na+, K+, Cl-, lactate dehydrogenase (LDH), creatine phosphokinase (CPK), and urine tests including dip-stick test and urine microscopy. Urinary human chorionic gonadotropin (hCG) level will be checked 14 days before the second visit for every participant with the possibility of pregnancy, experiencing lack of menstruation for less than 1 year since the last menstrual period.

**Figure 1 F1:**
[figure not shown]
The study design flowchart.

**Table 1 T1:**
[figure not shown]
The schedule of SOCG clinical trial.

### Participants and recruitment

2.2

One hundred forty eight participants in total will be competitively recruited in the Dunsan Korean medicine hospital of Daejeon university and the Chungnam national university hospital. Recruitment will begin in December, 2018 via advertisements in Daejeon subway stations, Dunsan Korean medicine hospital of Daejeon university, and Chungnam national university hospital.

#### Eligibility criteria

2.2.1

Inclusion criteria

(1)Age between 19 and 65 years.(2)Diagnosis of MDD per the Diagnostic and Statistical Manual of Mental Disorders – 5th edition (DSM-5).(3)Score >22 per the K-HDRS.(4)Decision to participate in the study and voluntary consent by signing the consent form.

Exclusion criteria

(1)Suicide risk.(2)Requirement of hospitalization.(3)Delusions, hallucinations, psychotic symptoms, or such a history.(4)Manic episodes, hypomanic episodes, mixed episodes or such a history.(5)Alcohol or other substance abuse/dependency issues or such a history.(6)Use of substances or drugs that may affect MDD symptoms (antianxiety drugs, antidepressants, antipsychotics, adrenocorticotrophic hormone drugs, estrogen preparations, L-dopa, digitalis, bromide, cyclosporine, disulfiram, isoniazid, yohimbine etc), unless 4 weeks have passed since the last use.(7)Hypokalemia or hypokalemia-inducible diseases (hypomagnesemia, Bartter syndrome, Gitelman syndrome, hyperaldosteronism inducible diseases, etc) or use of hypokalemia-inducible drugs (furosemide, thiazide, amphotericin, cisplatin, etc).(8)Use of warfarin.(9)Diagnosis of cardiac arrhythmia(10)Medical conditions that may affect the MDD symptoms (myocardial infarction, brain tumor, multiple sclerosis, pancreatic disease, hypo/hyperthyroidism, hyperparathyroidism, Addison's disease, Cushing's disease, Rheumatoid arthritis, cancer, cerebrovascular disease, dementia, epilepsy, etc).(11)Chronic diseases resistant to treatment (chronic active hepatitis, hypertension, diabetes mellitus, etc).(12)Treatment for hepatic tumor, hepatic cirrhosis, chronic renal failure, or congestive heart failure classified as New York Heart Association Class (NYHA Class) III–IV(13)Disabilities of hepatic or renal function (ALT, AST, ALP ≥ twice the upper limit of normal or creatinine > 2.0 mg/dL at screening).(14)Galactose intolerance, Lapp lactase deficiency, glucose-galactose malabsorption, or genetic problems.(15)Diseases that may influence drug absorption or digestive problems after associated surgery.(16)Participation in other clinical trials within the prior month.(17)History of hypersensitive or allergic reactions to drugs involved in the study.(18)Use of other herbal decoctions or extracts.(19)Difficulties in understanding the process of consent or in continuing to participate in the study due to mental retardation or cognitive problems.(20)Pregnancy or lactation.(21)Possibility of pregnancy and refusal to use contraceptive methods including double contraception^∗^, intrauterine contraceptive device, or spermicides during the study. ∗Double contraception is the use of barrier contraception (condom, diaphragm, etc) with other methods (sterilization surgery, intrauterine contraceptive device, contraceptive cream, jelly or foam).(22)Unsuitability for participation in the study due to other reasons.

### Randomization and blinding

2.3

One hundred forty eight participants will be equally divided into 4 groups. We will use stratified blocked randomization with the clinical trial institution as stratification variable. Each group will be distinguished using specific signs used in the randomization table. The signs and block size will not be disclosed. The randomization table will be re-creatable.

The product manufacturer Han kook shin yak corporate will prepare tablets based on the randomization tables. The tablets will be labeled as “Institution code-R-serial number” to be offered to the chief investigator and managed by the pharmacist responsible. The table matching the randomization table in terms of the serial numbers will be sealed and managed by the chief investigator. The seals will be amenable to examination to ascertain whether they have been removed. When the study physician requests administration of the preparation, the pharmacist will check the institution code and the serial number to assign the medication. The identification code will be recoded on the serial number table and managed by the pharmacist.

The participants, chief investigator, study physician, and coordinator will be unable to recognize the type of medication. Elimination of the blinding will only be considered in a severe medical emergency. When the investigator notices an absolute need for an emergency situation, the chief investigator will decide whether to eliminate the blinding through discussion. The chief investigator will be expected notify the removal and explain the detailed emergency situation to Institutional Review Boards (IRBs) of each institution within 24 hours.

### Interventions

2.4

SOCG is a brown rectangular film-coated tablet, containing 395 mg of SOCG soft extracts (Cyperi Rhizoma, Linderae Radix, Aucklandiae Radix, Glycyrrhizae Radix et Rhizoma, Platycodonis Radix, and Ponciri Fructus Immaturus). The control drug is an identically shaped tablet, containing only excipients.

SOCG or placebo will be administered orally, with water, 30 minutes after each meal, 3 times a day for 8 weeks (56 days).

Treatment groups:

(1)Low dose group: 1 tablet of SOCG and 2 tablets of placebo.(2)Medium dose group: 2 tablets of SOCG and 1 tablet of placebo.(3)High dose group: 3 tablets of SOCG.

Control group: placebo

(1)Placebo group: 3 tablets of placebo.

### Outcome measures

2.5

#### Primary outcome

2.5.1

The primary outcome will be changes in the K-HRDS score, comparing the baseline score and the last observed score during the eight weeks of treatment.

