#### Secondary outcomes

2.5.2

① Recovery of the K-HDRS (The percentage of participants whose K-HDRS improved >50%): Recovery in the last observed K-HDRS during the 8 weeks of treatment.

② Remission of K-HDRS (The percentage of participants whose K-HDRS improved to a score <7): remission in the last observed K-HDRS during the 8 weeks of treatment.

③ K-BDI-II: Changes in K-BDI-II comparing the baseline and the last observed score during the 8 weeks of treatment.

④ KSCL-95: Changes in KSCL-95 comparing the baseline and the last observed score during the 8 weeks of treatment.

⑤ ISI: Changes in ISI comparing the baseline and the last observed score during the 8 weeks of treatment.

⑥ STAI-K: Changes in STAI-K comparing the baseline and the last observed score during the 8 weeks of treatment.

⑦ STAXI-K: Changes in STAXI-K comparing the baseline and the last observed score during the 8 weeks of treatment.

⑧ Instrument on Pattern Identifications for Depression: Changes in Instrument on Pattern Identifications for Depression score, comparing the baseline and the last observed score during the 8 weeks treatment.

⑨ EuroQol-5 dimension (EQ-5D): Changes in the EQ-5D comparing the baseline and the last observed score during the 8 weeks of treatment.

10. Melatonin & Cortisol Study: Changes in the concentration of melatonin and cortisol comparing the baseline and the last observed score during the 8 weeks of treatment.

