#### Sample size

2.7.1

The sample size required is based on results of the t-test for independent samples comparing changes in the K-HRDS score from baseline to the last observed one during the 8 weeks of treatment between the SOCG medium dose group and the placebo group.

Because no relevant results of clinical trials have been reported, the sample size was calculated referring to a clinical trial of similar design involving patients with depression.^[15]^

The sample size of each group is 37, considering a significance level of 5%, a power of 80%, and assigning a ratio of 1:1:1:1 and a dropout rate of 5%.

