#### Statistical analysis

2.7.2

The efficacy will be evaluated based on intention-to-treat (ITT) analysis and per-protocol (PP) analysis. Participants with total drug compliance <75% will be excluded from PP analysis.

Continuous data will be represented by mean, standard deviation, minimum, and maximum and categorical data will be represented by a frequency table. We will compare data using analysis of variance (ANOVA) for the continuous variables, and Pearson chi-squared test or Fisher's exact test for the categorical variables. The size of the type I error caused due to multiple comparisons will be modified using Bonferroni's method.

The primary outcome, the changes in the K-HRDS, will be evaluated using analysis of covariance (ANCOVA) with the experimental group, baseline K-HDRS, and the institution as the explanatory variables. The estimates of mean differences between placebo and each SOCG group, the 95% confidence interval, and the *P*-value will be presented. For evaluating the sensitivity of missing values of K-HDRS, the primary outcome observed at each point will be analyzed using the linear mixed model. The explanatory variables include all groups, baseline K-HDRS, institutions, the observation time point, and the interaction term of the experimental group based on the observation time point.

Among the secondary outcomes, recovery rate and remission rate of K-HDRS will be analyzed using logistic regression analysis with the experimental group, baseline K-HDRS, and the institution as the explanatory variables. Estimates of odds ratio of each SOCG group, 95% confidence interval, and *P*-value will be presented using the placebo group as the standard category. The other secondary outcomes will be analyzed using ANCOVA with the experimental group, baseline outcomes, and the institution as the explanatory variables.

For safety assessment, outcomes of lab tests will be compared to the baseline values. Each adverse event will be listed with a detailed explanation, and the frequency will be recorded separately based on correlation with the medication. Adverse events will be summarized based on groups and organs. The ANOVA or Kruskal-Wallis test will be used to compare the frequency of medication-correlated adverse events between groups. The Pearson chi-squared test or Fisher's exact test will be used to compare the percentage of participants who experienced the adverse events at least once between the groups.

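### The primary outcome uses the last observed K-HDRS score, so dropout that differs by arm biases each dose–placebo difference; the week 8 contrast from the mixed model already planned should be primary

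*Protocol article*

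**What the plan says.** Protocol article, Primary outcome (2.5.1): the outcome is the change in K-HDRS "comparing the baseline score and the last observed score during the eight weeks of treatment". Sample size (2.7.1) uses the same endpoint, "comparing changes in the K-HRDS score from baseline to the last observed one during the 8 weeks of treatment", for the medium dose group against placebo, with one overall dropout rate of 5% and 37 per group.

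Statistical analysis (2.7.2): the primary outcome "will be evaluated using analysis of covariance (ANCOVA) with the experimental group, baseline K-HDRS, and the institution as the explanatory variables". The mixed model appears only as a check: "For evaluating the sensitivity of missing values of K-HDRS, the primary outcome observed at each point will be analyzed using the linear mixed model". Its terms are group, baseline K-HDRS, institution, "the observation time point, and the interaction term of the experimental group based on the observation time point".

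Secondary outcomes (2.5.2) follow the same rule. Recovery, for example, is "Recovery in the last observed K-HDRS during the 8 weeks of treatment", and remission and the change scores are defined likewise.

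The article gives no reason for ranking the last-observed analysis above the mixed model.

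**The concern.** For completers the last observed score is the week 8 score. For early leavers it is an earlier score used in its place, which is last observation carried forward written into the endpoint. If scores are still improving, early leavers are held at a less improved value, and the arm that loses more patients looks worse whatever the drug does. More loss on SOCG can hide an effect; more loss on placebo can create one. The method is therefore not reliably conservative.

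The trial is meant to choose a dose. Three dose groups are compared with one placebo group, and each contrast is shifted by its own dropout pattern. Equal dropout is not assured: the Discussion says SOCG has not yet been given to healthy people or patients, and lists possible effects such as diarrhea, dyspepsia and dizziness.

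**Working it through.** **The plan's own figure.** 35 evaluable per group with 5% dropout gives 35 / 0.95 = 36.8, rounded up to 37, which agrees with the plan. The article does not state the assumed difference and SD, so the 35 cannot be rebuilt. The bias below does not depend on it.

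**Inputs from the protocol:** 37 per group, 5% overall dropout, endpoint = last observed score within 8 weeks.

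**Assumptions, not in the protocol:** visits at weeks 2, 4, 6 and 8; dropout spread evenly after weeks 2, 4 and 6; the mean courses, SD and correlation given below.

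**Formula.** With dropout p in an arm and mean changes m2, m4, m6, m8, the expected last-observed change is (p/3)(m2 + m4 + m6) + (1 - p) m8.

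**1. True difference of -4, linear course to -12 on SOCG and -8 on placebo.**
- SOCG: early mean (-3 - 6 - 9)/3 = -6, so the expectation is -12 + 6p₁.
- Placebo: early mean (-2 - 4 - 6)/3 = -4, so the expectation is -8 + 4p₀.
- Difference: -4 + 6p₁ - 4p₀.

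| Dropout SOCG / placebo | Expected difference |
|---|---|
| 5% / 5% | -4 + 0.3 - 0.2 = -3.9 |
| 20% / 20% | -4 + 1.2 - 0.8 = -3.6 |
| 20% / 10% | -4 + 1.2 - 0.4 = -3.2 |
| 30% / 10% | -4 + 1.8 - 0.4 = -2.6 |

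The second row shows that balanced dropout also shrinks a true difference.

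**2. No true effect, 37 per arm, SD 6.5, common course to -9, two-sided 5% per comparison.**
- Linear course: early mean -4.5, so bias = 4.5(p₁ - p₀).
- Decelerating course (40%, 70%, 90%, 100% of the final change): early mean -6, so bias = 3(p₁ - p₀).
- An average of 5% over two arms is 0.05 × 74 = 3.7, about 4 patients.

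| Patients lost, one arm v the other | Bias, linear (type I error) | Bias, decelerating (type I error) |
|---|---|---|
| 3 v 1 of 37 | 4.5 × 2/37 = 0.24 (about 5.3%) | 3 × 2/37 = 0.16 |
| 4 v 0 of 37 | 4.5 × 4/37 = 0.49 (about 6.2%) | 3 × 4/37 = 0.32 (about 5.5%) |
| 30% v 10% (stress case) | 4.5 × 0.20 = 0.9 (about 9%) | 3 × 0.20 = 0.6 (about 6.8%) |

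For the linear 30% v 10% case, 20,000 simulated trials with AR(1) correlation 0.7 gave a bias of 0.91 and a type I error of 8.7%. With the loss reversed (placebo 30%, SOCG 10%) the bias was -0.89, and false wins for SOCG came to 7.9% against a nominal 2.5%.

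With the true difference of -4 from step 1, a 4 v 0 split gives 6 × 4/37 = +0.65 if all the loss is on SOCG and -4 × 4/37 = -0.43 if all is on placebo.

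**3. Dose comparison.** Under step 2's linear course, doses j and k are shifted relative to each other by 4.5(pⱼ - pₖ), so their apparent order can change through dropout alone.

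**4. A second set of assumptions.** Two arms of 37, placebo course -4, -7, -9, -10, SD 7.5, AR(1) 0.7, and 2,000 trials per scenario. Dropout was either unrelated to scores or dependent on observed scores. A t-test stood in for the ANCOVA, and sequential regression on the observed visits stood in for the mixed model.
- Last-observed estimate: off by about 0.2 to 0.7 points at 2% v 10% dropout, and by about 0.6 to 1.6 at 10% v 30%, taking true differences of 0 and -5 together.
- Type I error at 10% v 30%, in either direction: 6.0% to 9.2%.
- Week 8 likelihood estimate: within about 0.1 points of the truth throughout (Monte Carlo standard error about 0.04).

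**The case against.** The plan does recognise missing data. The mixed model has suitable terms and will be run, so the dispute is over which analysis is primary. At the planned 5%, about two patients per arm, the error is about 0.1 points if balanced. The large figures need 30% v 10% dropout, which nothing in the protocol suggests, and a decelerating course cuts that null bias from 0.9 to 0.6. All of this stands and limits the size of the point. It does not justify the ranking: the primary analysis carries the claim, and actual dropout by arm is unknown.

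Three stronger readings are tempting, and the protocol does not support them.
- **That the result will be seriously biased, or type I error will reach 9%.** That is a stress case. The protocol gives one overall rate and no arm-specific rates.
- **That the ANCOVA's standard error is wrong because imputation uncertainty is ignored.** The endpoint is defined as the last observed score, which is an observed quantity. The fair objection is to its relevance as a week 8 effect.
- **That recovery and remission are put right by counting every missing week 8 score as a failure.** An early leaver can indeed count as recovered under the present rule. But non-response is also a single imputation, and it also penalises the arm with more dropout. It is at most an optional convention.

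**Conclusion.** The point holds as one about the choice of primary analysis. The last-observed endpoint is biased for the week 8 effect when scores are still changing and dropout differs by arm. The direction depends on which arm loses more. It is confidently right in principle and modest in expected size: near the planned 5% dropout the bias runs from about 0.1 points (balanced, true difference -4) to about 0.3 to 0.5 (all in one arm, no true effect). It is somewhat more, 0.65 by the same formula, if all the loss is on SOCG and the true difference is -4. Every size rests on assumed visit times and mean courses, and the error rates also on an assumed SD. The advantage of the mixed model rests on missing at random. The change is worth making because a less biased analysis is already planned.

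**What to change.** - Define the primary outcome as the change in K-HDRS from baseline to week 8.
- Make the group contrasts with placebo at week 8, from the planned linear mixed model (group, baseline, institution, time, group-by-time), the primary analysis. Name the time point: the model has a group-by-time term, and the Discussion mentions a follow-up four weeks after treatment.
- Keep the last-observed ANCOVA as the sensitivity analysis.
- Align the endpoint wording in Sample size (2.7.1). The number per group need not change on this account.
- If missing week 8 scores are counted as non-response for recovery and remission, state this as a convention and not as a cure for unequal dropout.

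**Cost.** No new visits, data or patients. It does redefine the primary outcome of a trial that the Discussion describes as already recruiting. It must therefore be made before unblinding and notified to the IRBs, as the ethics section (2.9) requires for protocol modifications. The statistical price is that the primary result relies on missing at random; a sensitivity analysis for departures from that assumption would be a useful addition.
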